### Intervention

Caregivers in the intervention condition will receive the MOMANT manual-based training and support program consisting of multiple components, including special attention for the implementation of activities at home: 1) educating caregivers on effective communication with the person with dementia; 2) teaching skills of how to manage difficult behaviour of the person with dementia; 3) suggesting methods of how to cope with the burden of caregiving; 4) providing detailed suggestions of how to engage the person with dementia in activities that are enjoyable and stimulating, physically, cognitively or socially in a person-centred way. That is, the activities should match the interests and abilities of the person with dementia and the caregiver and may include activities such as household tasks, going over news headlines, reminiscence activities, walking or other simple physical activities. As such, the manual consists of an overview of these topics, details of activities and examples of materials to be used in activities, and additional information, e.g., useful website links and telephone numbers on where to find and how to use available health services. Education and training of caregivers will take place in small groups (4–8) at the day care centres, led by a health care professional, during 6 sessions over 2 months. Each session will last approximately 1 h. The first 3 sessions will be held weekly, the subsequent 3 sessions will be held with intervals of two weeks.

Although the precise content of the sessions will in part be determined by caregivers’ needs and wishes, the program consists of the following sessions:Introduction and explanation rationale and goal of the training, education on different types of dementia and the consequences, and general suggestions for a healthy lifestyleStress of caregiving and coping strategies to reduce behavioural disruptions in people with dementia, and practicing communication techniquesHow to present the activities, basic principles and how to motivate the person with dementiaImplementation of activities at homeCaregivers’ experience of presenting activities at home, discuss difficulties and possible solutionsCaregivers’ overall experience with the intervention, revisit topics presented in earlier sessions

From meeting 3 onwards, caregivers will be encouraged to start with activities at home with the person with dementia. During the remaining sessions, time will be reserved for feedback from caregivers and further support on how to implement activities at home.

The caregiver training will take place at day care centres for people with dementia and their caregivers. The participating caregivers will attend a day care centre in their area to join the training, which provides the opportunity that the person with dementia is looked after if needed, while their caregiver is attending the training.

To facilitate implementation of the intervention at home and to assess intervention fidelity, the health care professional who provides the training will also visit the dyad once at home. This visit will be scheduled to provide the caregiver with an individual session to ask questions as opposed to the group sessions and to allow the professional to see how the activities are performed at home. The health care professional will advise on how to implement the activities at home over a longer term. After the visit the professional will rate how well the caregiver presents the activities at home as part of the assessment of intervention fidelity.

Health care professionals involved in the study will themselves be trained by the research team on how to offer the intervention. As these professionals already have extensive experience in dementia care, this training of the trainers will take place in a single session of 2 to 2.5 h. In this session, trainers will also receive a copy of the manual for caregivers, which is the basis for the caregiver training, and a trainer’s manual which outlines the content of the intervention sessions.

The manual for caregivers and trainers will be adopted from material developed earlier (Milders, Bell et al. [26], Milders, Bell et al. [25]). Finalising the manual content will also occur in consultation with caregivers, people with dementia, and professionals in dementia care as part of the focus group that will be set up at the start of the study.

### Treatment as usual

Participants in the control condition will continue to receive treatment and care as usual. Common practice regarding dementia care in the Netherlands varies between regions, but most community-dwelling persons with dementia are cared for by their spouse or relative in their own home, and attend day care facilities outside their home one or more days per week. Participants randomised to the control group can continue with any health, social or voluntary sector services they are currently receiving or commence once recruited into the study. Participants who are allocated to the control condition will also be offered the opportunity to receive the intervention material after completion of the final assessment.

### Measures

Data from participants in the intervention and control conditions will be collected by trained researchers on three occasions, i.e., at baseline, prior to the start of the intervention; 3 months after baseline; and 6 months after baseline. Nursing home admission will be recorded until shortly before the study ends by means of a telephone conversation with the caregiver 12–18 months after the final assessment.

The primary outcome is health-related quality of life for the caregiver. Secondary outcomes for the caregiver include the caregivers’ feeling of competence to care for the person with dementia, caregivers’ experience of caregiving, and mood. The primary outcome for the person with dementia is self-reported quality of life. Secondary outcomes for the person with dementia include activities of daily living, global functioning, and the frequency of activities enjoyed by the person with dementia; as reported by the caregiver. Participants are also asked about health resource use and caregiver time inputs to explore cost-effectiveness.

### Primary outcome

The primary outcome measure for the caregiver will be health-related quality-of-life assessed with the self-reported EQ-5D-5L instrument, including visual analogue scale (VAS) (Herdman, Gudex et al. [20], Versteegh, Vermeulen et al. [52]). The descriptive system comprises five dimensions: mobility, self-care, usual activities, pain/discomfort and anxiety/depression, scored on a five-point scale. A higher score corresponds to more severe complaints, and thus a lower quality of life. The EQ-5D-5L has proven to be a valid and reliable questionnaire to measure quality of life in several populations (Janssen, Birnie et al. [22], Feng, Kohlmann et al. [13]), and the VAS has shown good convergent validity (Tran, Ohinmaa et al. [48]).

The primary outcome measure for the person with dementia will be quality of life assessed with the self-reported Dementia Quality of Life scale (DQOL; (Brod, Stewart et al. [3]) comprising of 29 items, ranked on a five-point Likert scale and measuring five QoL domains: self-esteem, positive affect, negative affect, feeling of belonging and sense of aesthetics. A higher score on the DQOL means a better quality of life, except on the negative affect outcome. The questionnaire has shown good internal consistency, and good convergent validity (Wolak-Thierry, Novella et al. [57]). The DQOL is an appropriate research tool for people with dementia, because it has been used extensively in this population, and has proven good discriminant validity (Wolak, Jolly et al. [58], Wolak-Thierry, Novella et al. [57]).

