#### Eligibility criteria

Informal caregivers can be spouses, relatives, or friends who care for and support the person with dementia without receiving payment for performing care. If the caregiver does not live with the person with dementia, they have to visit the person with dementia at least 3 times a week to be eligible for the study.

The person with dementia is living at home, cared for by the caregiver, and should have a formal diagnosis of dementia or experience severe cognitive impairments influencing their daily functioning such that dementia is strongly suspected. Type of dementia is not an inclusion criterion. The person with dementia did not start with dementia-specific medication less than 6 months before inclusion.

Exclusion criteria for both the caregiver and the person with dementia will be major mental or physical illness, such as major depression or stroke, that would affect their ability to participate in the training, the intervention or complete the assessments. A second exclusion criteria will be participation in another intervention study.

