Pleasant events: the Pleasant Events Schedule-Alzheimer’s Disease (PES-AD; Teri and Logsdon (Teri and Logsdon [45]) Short Form is a commonly used self-report assessment that attempts to identify activities that individuals with dementia may find enjoyable. It is used to assess the overall frequency of engagement in 20 activities by the person with dementia, as reported by the caregiver. A higher score indicates that the person with dementia is engaged in and enjoyed more activities. The PES-AD had good predictive validity, and most participants endorsed the majority of items indicating that this measure accurately identified items that are likely to be enjoyable by older adults (LeBlanc, Raetz et al. [24]).

Activities of daily living: Interview for Deterioration in Daily Living Activities in Dementia (IDDD; Teunisse and Derix (Teunisse and Derix [47]), a caregiver-based measure which consists of 33 items, reflecting the initiative to perform and actual performance of self-care and more complex activities, as reported by the caregiver. A higher score indicates more cognitive impairment in daily life. The IDDD has good construct validity and test–retest reliability (Voigt-Radloff, Leonhart et al. [53]).

Global functioning: Global Deterioration Scale (GDS; Reisberg, Ferris et al. [38]) denoting presence and severity of dementia. The GDS identifies seven stages of severity (1 least severe – 7 most severe) based on the estimated amount of cognitive decline. The GDS is completed in a structured interview with the caregiver. The GDS has been reported to have good interrater reliability, ranging from 0.82 – 0.92 (Wesson and Luchins [54]).

Time of admission to residential care, as reported by caregiver.

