#### Patient outcome analysis

Societal costs will be related to the following effect measures in the economic evaluation:

(i) quality-adjusted life-years (QALYs) based on the Dutch tariff for the EuroQol (EQ-5D-5L; Group [17]) at the level of the caregiver; (ii) quality of life of the person with dementia using the Dementia Quality of Life scale (DQoL). The analysis will be performed according to the intention-to-treat principle. Missing cost and effect data will be imputed using multiple imputation. Incremental cost-effectiveness ratios (ICERs) will be calculated by dividing the difference in mean total costs between the treatment groups by the difference in mean effects. Bootstrapping with 5000 replications will be used to estimate the 95% confidence intervals around cost differences and the uncertainty surrounding the ICERs. Uncertainty surrounding the ICERs will be graphically presented on cost-effectiveness planes. Cost-effectiveness acceptability curves showing the probability that the intervention is cost-effective in comparison with usual care for a range of different ceiling ratios will also be estimated.

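### Dementia severity should be a fixed term in the DQOL model and its imputation model, because the DQOL is a self-report and entry has no explicit severity ceiling

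*Protocol article*

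**What the plan says.** All references are to the protocol article.

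- **Primary outcome.** For the person with dementia this is "quality of life assessed with the self-reported Dementia Quality of Life scale", "comprising of 29 items, ranked on a five-point Likert scale and measuring five QoL domains". The article supports the choice in general terms: "The DQOL is an appropriate research tool for people with dementia, because it has been used extensively in this population". It gives no severity range for that statement, and no rule for a person who cannot answer.
- **Eligibility criteria.** The person "should have a formal diagnosis of dementia or experience severe cognitive impairments influencing their daily functioning such that dementia is strongly suspected". No stage or cognitive score closes entry at the severe end. The exclusion, which applies to both members of the dyad, is "major mental or physical illness, such as major depression or stroke, that would affect their ability to participate in the training". The same sentence goes on to name the intervention and completion of the assessments.
- **Secondary outcomes.** A first-visit question asks about mental or physical problems that could get in the way of taking part. Severity is measured on the Global Deterioration Scale (GDS): "The GDS identifies seven stages of severity (1 least severe – 7 most severe". It is obtained by interview with the caregiver and is not used for entry.
- **Data management / statistical analysis.** The effect analysis is an intention-to-treat linear mixed model. No imputation is stated for it. Apart from baseline scores, covariates enter only if the arms are found to differ on them at baseline and they are related to the outcome.
- **Patient outcome analysis.** The DQOL is one of two effect measures in the economic evaluation, and "Missing cost and effect data will be imputed using multiple imputation". No exception is made.
- **Sample size.** The calculation covers the primary outcomes of both dyad members: 64 completing dyads per arm, 85 recruited per arm after 25% drop-out.

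**The concern.** A caregiver can stay in the study while the person with dementia cannot answer 29 Likert items, at baseline or by 6 months. That dyad completes the study but yields no DQOL score at that visit. The reason is plausibly the severity of the dementia, which may also relate to quality of life and to how it changes.

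Two analyses then depend on an assumption of missingness at random given what is in the model. The mixed model needs it for people who lose the ability to report during follow-up. The economic imputation needs it for every missing DQOL, including those of people who never gave one. If severity is left out of either model and DQOL completion differs between arms, the estimated difference can be biased. The Discussion section accepts that cluster randomisation may leave the arms different at baseline, though it does not name severity.

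The covariate rule tests the wrong property. A variable can be balanced between arms and still be the main predictor of who has a score. The rule's second condition, a relation with the outcome at baseline, can be checked only in people who gave a baseline DQOL, so it leaves out those for whom the question matters most.

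**Working it through.** **1. Does the exclusion close the gap?** Read in full, the exclusion does reach people who could not complete the assessments. Its cause is limited to major mental or physical illness, with depression and stroke as examples. Dementia is the inclusion condition, so the natural reading is illness other than dementia. The criterion also applies at entry and says nothing about decline over 6 months. It is a partial screen.

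**2. Where does a missing DQOL go?**

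| Analysis | Treatment of a missing DQOL | Is severity conditioned on? |
|---|---|---|
| Linear mixed model | Observed scores only; no imputation stated | Only if the arms differ on it at baseline and it relates to the outcome |
| Economic evaluation | Multiply imputed, no exception | Not stated |

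**3. The plan's own sample size.** Inputs: difference 0.5 SD, alpha 0.05 (two-sided assumed, since sidedness is not stated), power 80%.

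- Normal approximation: n per arm = 2 × (1.960 + 0.842)² / 0.5² = 62.8, so 63.
- Exact two-sample t-test: 63.8, so 64. Power at 64 is 0.801. The stated 64 is reproduced.
- Drop-out: 64 / 0.75 = 85.3, so 86 strictly, against 85 stated; 85 × 0.75 = 63.75. The difference is immaterial.

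The point does not rest on an error in this figure.

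**4. Illustration of lost DQOL scores.** Let u be the share of completing dyads in which the person cannot give a DQOL, over and above the 25% drop-out. The article gives no value, so u is assumed. DQOL values per arm = 64 × (1 − u); power is from the t-test at d = 0.5, ignoring clustering.

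| Assumed u | DQOL values per arm | Power |
|---|---|---|
| 0% | 64 | 0.801 |
| 10% | 57.6, about 58 | 0.761 |
| 20% | 51.2, about 51 | 0.706 |
| 30% | 44.8, about 45 | 0.650 |

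The size of any bias cannot be calculated from the article. It would need the completion rate by severity and arm, and the relation of severity to DQOL change.

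**The case against.** The case on the other side has real content.

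- **Late-stage entry is less likely than the bare criteria suggest.** The person must live at home and is recruited mainly through day care centres. The exclusion mentions completing the assessments, and the first-visit question is broader than major illness. Under Consent, the caregiver may consent on the person's behalf only for impaired vision or writing; no route is given for cognitive incapacity. This stands. A reader might infer from the seven GDS stages that sites would enrol people in the last stages, but the scale's range describes the instrument, not the sample. None of these provisions deals with decline after baseline.
- **The mixed model uses observed scores.** A reader might infer that the effect comparison counts people who cannot report the DQOL. The article does not support that. Including everyone who entered does not mean that unobserved scores are filled in, and multiple imputation is stated only for the economic evaluation. A person with no DQOL score adds no DQOL information to the mixed model.
- **Severity can already enter as a covariate.** Clinical characteristics are compared at baseline, and those meeting the rule are adjusted for. This is true when an imbalance is detected. It does not help when severity is balanced but predicts missingness.
- **The imputation model may be set out in an analysis plan that is not shown.** That stands, and its absence here is not the finding. The covariate rule is stated in the article itself.
- **The 25% drop-out allowance may already include people who cannot be assessed.** Nothing in the article settles this, so the power figures are illustration only.

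**Conclusion.** The point holds as a weakness in how the DQOL analyses are conditioned. The article combines a self-reported primary outcome with no explicit severity ceiling, imputes missing effect data in the economic evaluation without exception, and lets severity into the models only through a baseline-balance rule. The missing-at-random assumption is weaker than it need be, when a caregiver-reported severity measure is already available for people who cannot answer.

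It does not show that the DQOL effect estimate is biased, that many participants cannot self-report, or that the sample size is wrong. That inability rises with severity is a plausible assumption, not something the article reports. The fall in power to about 76%, 71% or 65% depends wholly on the assumed 10%, 20% or 30%, on that loss being additional to drop-out, and on ignoring clustering.

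**What to change.** 1. Prespecify baseline GDS stage as a fixed term in the DQOL mixed model and in the DQOL imputation model, whatever the observed baseline balance. For this outcome it takes severity out of the balance-based covariate rule.
2. Report DQOL completion at each visit by arm and baseline GDS stage.
3. Add a sensitivity analysis of the DQOL cost-effectiveness result that does not impute the DQOL for people who gave none at baseline.
4. State that the DQOL conclusion applies to people able to self-report.

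Keep the intention-to-treat set as the main analysis. Restricting the main comparison to people who completed the DQOL at baseline would depart from the article's own principle, would also drop people whose baseline score is missing for other reasons, and would not show that the recorded answers are valid.

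The cost is analysis and reporting wording, a few model degrees of freedom, one extra economic analysis and a narrower claim for this outcome. No new instrument, visit or staff is needed. Enrolment is unaffected, which matters because the article expected data collection to end by December 2021. The change should be fixed before DQOL results are seen by arm.

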### Secondary outcomes

The Resource Utilization in Dementia (RUD; Wimo, Gustavsson et al. [55]) will be used to collect socio-demographic characteristics of the caregivers and persons with dementia including age; gender; relationship with person with dementia; employment status; and living situation. Furthermore, additional questions regarding the in- and exclusion criteria will be asked during the first visit: dementia diagnosis related information, whether major events occurred in the last 3 months that might affect well-being, whether they have mental or physical problems that might hinder participation, and whether they receive any other support or training through another intervention of the day care centre.

Sense of competence: The Short Sense of Competence Questionnaire (SSCQ; Vernooij‐Dassen, Felling et al. [51]) is a seven-item questionnaire that specifically measures a caregiver’s satisfaction and worries in their role as caregiver. In this shorter version the items refer to three domains: the satisfaction of the caregiver with the person with dementia as recipient of care; the satisfaction of the caregiver with their own performance as caregiver; and the negative consequences that caring has for the social and personal life of the caregiver. The three subscales showed good homogeneity and feasibility, also when comparing the population of informal caregivers of patients with diagnosed dementia with the caregivers of older adults with dementia symptoms (Jansen, van Hout et al. [21]). A higher score indicates less sense of competence in dealing with the burden of caregiving.

Positive experiences through informal care: Positive Experiences Scale (PES; De Boer, Oudijk et al. [10]) consist of eight items to measure positive experiences by informal caregivers. It varies from intrinsic satisfaction and relational enhancement to improvement of competence and social enhancement. For caregivers of persons with dementia, the authors of the PES recommend to exclude two items (‘because of the caregiving the relation with my family and friends has become closer’ and ‘I receive a lot of appreciation for the care I gave’), because these do not apply to informal caregiving of dementia. The total score is calculated by adding up all individual scores, where a higher score indicates a more positive experience towards caregiving. The PES had good reliability (α = 0.74) and is recommended because of its psychometric qualities and its usefulness in different populations of informal caregivers (De Boer, Oudijk et al. [10]).

Mood: The Center for Epidemiologic Studies – Depression (CES-D1; Radloff (Radloff [37])is a brief self-report scale designed to measure self-reported symptoms associated with depression experienced in the past week. It consists of 20 items comprising six scales reflecting major facets of depression: depressed mood, feelings of guilt and worthlessness, feelings of helplessness and hopelessness, psychomotor retardation, loss of appetite, and sleep disturbance. A higher score means the presence of more depressive symptoms. The CES-D1 does not measure chronic depression, but current levels of depressive symptomatology, and demonstrated strong internal consistency with Cronbach’s α ranging from 0.79 to 0.90 in caregiving and other medical studies (Clark and Diamond [8]).

Use of health care: An adapted version of the RUD (Wimo, Gustavsson et al. [55]) will be used to measure healthcare resource utilization among persons with dementia and their caregivers, and time spent on formal and informal care by caregivers. The RUD is a widely used instrument to assess resource use in dementia. The RUD will be completed by the caregiver’s report on healthcare resource utilization of themselves and of the person with dementia.

Pleasant events: the Pleasant Events Schedule-Alzheimer’s Disease (PES-AD; Teri and Logsdon (Teri and Logsdon [45]) Short Form is a commonly used self-report assessment that attempts to identify activities that individuals with dementia may find enjoyable. It is used to assess the overall frequency of engagement in 20 activities by the person with dementia, as reported by the caregiver. A higher score indicates that the person with dementia is engaged in and enjoyed more activities. The PES-AD had good predictive validity, and most participants endorsed the majority of items indicating that this measure accurately identified items that are likely to be enjoyable by older adults (LeBlanc, Raetz et al. [24]).

Activities of daily living: Interview for Deterioration in Daily Living Activities in Dementia (IDDD; Teunisse and Derix (Teunisse and Derix [47]), a caregiver-based measure which consists of 33 items, reflecting the initiative to perform and actual performance of self-care and more complex activities, as reported by the caregiver. A higher score indicates more cognitive impairment in daily life. The IDDD has good construct validity and test–retest reliability (Voigt-Radloff, Leonhart et al. [53]).

Global functioning: Global Deterioration Scale (GDS; Reisberg, Ferris et al. [38]) denoting presence and severity of dementia. The GDS identifies seven stages of severity (1 least severe – 7 most severe) based on the estimated amount of cognitive decline. The GDS is completed in a structured interview with the caregiver. The GDS has been reported to have good interrater reliability, ranging from 0.82 – 0.92 (Wesson and Luchins [54]).

Time of admission to residential care, as reported by caregiver.

